## Trial intervention

### HIV infant tracking system

The HITSystem was designed to overcome barriers in providing high quality EID in low-resource settings by utilizing available technology to facilitate timely communication and accountability between primary stakeholders in the EID process. The primary goals of the HITSystem are the following: to (a) improve EID utilization and clinical management of HIV-exposed infants, (b) facilitate early ART initiation for infants identified as HIV-infected, and c) improve efficiency in providing time-sensitive interventions. The HITSystem is accessed online through a computer, using mobile broadband connections. Reliance on cellular signals (readily available and reliable in nearly all areas) rather than hard wired internet access makes this system feasible even in remote areas. The primary components include the following: (1) tracking of infants to increase retention, (2) action alerts to complete time-sensitive interventions, (3) real time communication of PCR lab results to hospitals, and (4) real time communication with mothers regarding required follow-up care via text messaging or patient tracing.

The HITSystem tracks the care of infants enrolled in EID so that those who drop out of care can be easily identified and targeted for outreach. Using the infant’s date of birth, the HITSystem configures automated electronic alerts for eight time-sensitive interventions to optimize care for HIV-exposed infants. The order and timing of these action alerts have been previously published [21]. PCR test results entered into the online system from the lab become available to hospitals in “real time” thus eliminating the need for costly and unreliable couriers to transport paper results. Excessive delays for laboratory test results are also targeted by triggering alerts at the laboratory for samples received but not tested within 10 days. When results are available, mothers are sent an Short Message Service (SMS) message asking them to come to the hospital at their earliest convenience. Text messages do not relay sensitive information that could compromise confidentiality. In the case of indeterminate results, mothers are notified to return with infants to collect another sample. To address one of the weakest areas of current EID care, the HITSystem proactively texts mothers when re-testing of infants is due at 9 and 18 months of age. Infants enrolled in the HITSystem are tracked until they are either (a) conclusively determined HIV negative at 18 months and discharged from EID, (b) determined to be HIV-infected, initiated on ART, and linked to pediatric HIV care, or (c) dead or transfered to another health facility.

#### HITSystem staffing

At each participating hospital, the EID provider enters relevant data into the HITSystem during initial enrollment and subsequent visits. EID providers at each hospital monitor and respond to the action alerts for enrolled infants and coordinate participant tracing for those mothers without phones. This process is supported by a Research Coordinator at each intervention site. At laboratories, one to two technicians are trained on the HITSystem and serve as a liaison for follow-up requests made by EID staff or the Research Coordinator. The Study Manager reviews action alerts to identify systematic challenges across hospitals, provide quality assurance with data collection, and provide refresher training with hospital and lab-based staff every 6 months or earlier as needs arise due to program modifications or personnel changes. Once deployed, the HITSystem will continue in the setting until the end of the study. A phase-out plan will be implemented to maximize adoption among site staff and sustained use after the study period.

### Training at study sites

#### Control sites (standard of care)

There is no training or intervention regarding EID procedures at control sites. Nurses directly involved in EID enrollment were trained to assess participant eligibility, to conduct informed consent, and administer the brief baseline survey. The same nurses were trained on procedures to ensure participant confidentiality and secure storage of study data.

#### Intervention sites (HITSystem)

Training for providers began with a discussion of the challenges and barriers to EID care and an introduction to how the HITSystem is designed to tackle these issues; doing this was designed to promote buy-in from the facility staff and generate enthusiasm about the introduction of a new tool. The intuitive and user-friendly nature of the HITSystem allows training of key clinic/laboratory personnel in 1 to 2 days. During initial training, new users were educated about the HITSystem’s standard operating procedures, and hands-on data entry scenarios were used to tailor training of each staff member to the specific capacity in which s/he would utilize the HITSystem. Research team members received extensive HITSystem training to ensure their ability to respond effectively to any user-challenges and provide refresher training as needed. Furthermore, they receive ongoing training on study protocols, informed consent, and data collection and data management procedures to ensure rigorous conduct of the study protocol.

### Participant enrollment

When a mother first presents her infant for EID, the EID provider creates a new infant record in the EID Registry notebook (SOC) or the HITSystem (intervention), and data regarding her antenatal care, maternal ARV prophylaxis regimens, and postpartum infant prophylaxis are entered. The mother’s cell phone number is also recorded in the HITSystem at this time. The majority of mothers have cell phones (97 % in urban and 82 % in peri-urban pilot hospitals) ([name] et al., Lessons learned from implementing the HIV Infant Tracking System (HITSystem) to improve early infant diagnosis of HIV outcomes in Kenya, submitted) [22], but for the few mothers without access or who prefer not to use their cell phones, we ask for a hand drawn map from the clinic to their home or major landmark to assist follow-up efforts. At subsequent consultations (PCR test results, 9 month re-testing, etc.), the infant’s information is updated in the EID Registry notebook (SOC) or pulled up electronically on the HITSystem and populated with additional data (intervention).

### Fidelity assurance procedures

Standard operating procedures were developed for each step of the study process to standardize training, enrollment, and all data collection procedures. Because it is web-based, the intervention features remain uniform across all sites utilizing the HITSystem. Furthermore, any modification or corrections to the HITSystem are instantly applied across all users. HITSystem entries are routinely reviewed to ensure completeness and appropriate utilization of the comments section. Site Coordinators make monthly visits to the control sites to cross reference enrollment records with the EID Registry and to review informed consent documents and surveys for completeness and secure storage. A random sub-sample of informed consents and surveys are reviewed by the Study Manager for accuracy and completeness at each site.

### Randomization

Prior to randomization, 12 hospitals were surveyed to determine the location, patient volume and HIV prevalence (through review of EID Registry for prior 12 months), consistency in current EID procedures, and feasibility of study procedures. Using these data, six sites with the most comparable characteristics and regional location were selected. All individuals enrolled in the study at each hospital comprised the unit or cluster for randomization. A random number generator program was then used to randomly assign control and intervention sites within a given geographical region. Study statistician was blind to the process of choosing the sites. Similarly, all research staff was blind to the randomization process.

### Study measures and data sources

This system-level intervention is implemented at the site level, but outcome measures pertain to both the participant and cluster level. Primary data collection efforts include the following: (1) retrospective data collection of EID outcomes prior to study implementation, (2) baseline surveys at the time of enrollment, (3) ongoing collection of EID outcome data during the study period, (4) satisfaction surveys with mothers and providers, and (5) collection of EID-related costs.

#### Retrospective data

Research Coordinators conducted a thorough retrospective record review of the EID Registry at each hospital to document EID outcomes (Table 1) during the 12 months prior to study implementation. Supporting medical records (described in the primary EID outcome section below) were used to complete missing data points in the EID Registry.

#### Baseline surveys

A brief, one-time baseline survey was conducted with each mother at the time of EID enrollment at intervention and control sites. Surveys collected basic demographic data and a variety of potential baseline predictors of EID retention, including the following: EID knowledge, stigma/violence, motivation and self-efficacy for completing EID, partner support, disclosure, distance and cost to the hospital, income, education, and number of children.

#### Primary EID outcomes

The HITSystem output provides infant date of birth, dates of services (sample collection, sample processed and result posted, notification of mother, treatment initiation or re-testing as applicable, discharge), and outcomes of service (infant test results at each time period, initiation of ART, reason for discharge). To assess the standard provision of EID care at control sites, all infants entered in the HIV-Exposed Infant Registry Book each month during the enrollment period are reviewed until the sample size of *n* = 120 mother-infant dyads is achieved per control site. Consistent with the strategy employed and deemed feasible in the pilot study [21], and used for the retrospective data collection, we cross reference the following sources: (1) infant medical records, (2) hospital HIV-Exposed Infant Registry, (3) Clinical Care Center (CCC) records, and (4) central laboratory PCR database to permit parallel assessment of the outcomes collected by the HITSystem. The following EID outcomes are measured at all sites.

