##### Timely delivery of EID Services

For each of the 8 EID intervention points (Table 1), we will create an Optimal EID Care Index to measure whether the service was completed at all (1 point) or never completed (0 point) and whether it was completed on-time (1 point) or off-time (0 point). For each EID intervention point, each mother-infant dyad may receive either 0 point (never completed), 1 point (off-time completion), or 2 points (on-time completion). From these data, we will create an Optimal EID Care Index score for each dyad by summing across the 8 EID intervention point scores (range of 0–16 points). Dyads receiving a minimum score of 0 will have completed none of the 8 EID intervention points. Dyads receiving a maximum score of 16 will have completed all 8 points on-time. Scores between 0 and 16 will reflect some combination of completion and on-time completion.

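### Outcomes are taken from different sources in the two arms, so a difference in documentation can pass for a treatment effect, mainly on mother notification, OI prophylaxis and negative antibody re-tests

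*Protocol article*

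**What the plan says.** The Primary EID outcomes section names one source per arm. For intervention hospitals, "The HITSystem output provides infant date of birth, dates of services" and the outcomes of those services. Under HITSystem staffing, "the EID provider enters relevant data into the HITSystem during initial enrollment and subsequent visits"; the same provider monitors and responds to the action alerts.

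For control hospitals the section reads "To assess the standard provision of EID care at control sites, all infants entered in the HIV-Exposed Infant Registry Book each month" of the enrollment period are reviewed until 120 dyads are reached. It continues: "we cross reference the following sources: (1) infant medical records, (2) hospital HIV-Exposed Infant Registry, (3) Clinical Care Center (CCC) records" and, fourth, the central laboratory PCR database, "to permit parallel assessment of the outcomes collected by the HITSystem". It adds that the same outcomes are measured at all sites, which fixes the outcomes but not their source.

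Participant enrollment confirms the split at the point of recording: the provider "creates a new infant record in the EID Registry notebook (SOC) or the HITSystem (intervention"), and later visits are recorded in the same arm-specific place.

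Under Fidelity assurance procedures, HITSystem entries are routinely reviewed for completeness. The checks described at control sites concern enrollment records, consents and surveys; service entries are not named.

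**The concern.** The intervention is also the instrument that records the outcome in one arm. The article expects it to change record-keeping: the Background lists documentation among the problems of usual care, and the cost paragraph under Qualitative analyses counts better record-keeping among the expected gains. If a delivered service is more likely to be found in one arm's records than in the other's, the comparison mixes care with documentation.

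Retention is sensitive to this because it is all-or-nothing: one missing step makes a dyad incomplete. The Optimal EID Care Index is also affected, since it gives 0 for a service never completed and a further point only if the service was on time, which needs a date. Randomizing hospitals does not remove a difference in ascertainment that follows the allocation.

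**Working it through.** **Which steps are exposed.** The plan states no figure to reproduce, so the first check sets the steps against the control-arm sources.

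- PCR sample and result dates: the laboratory PCR database should hold these for samples that reached the laboratory. Largely protected.
- ART start: CCC records should hold this. Largely protected.
- Mother notification: under Standard of care, a mother whose infant is PCR-negative is told at a later clinic visit. No laboratory or CCC record would show this. Exposed.
- Re-tests at 9 and 18 months: these are antibody tests, with PCR only after a positive result. A negative re-test leaves no PCR record. Exposed.
- OI prophylaxis: it has no laboratory record. Exposed; it counts in the Care Index but not in the retention definition.

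For an uninfected infant, retention needs four steps (DBS, notification, two re-tests), and three of them are exposed. In the Care Index, four of the eight items are exposed, worth up to 4 × 2 = 8 of 16 points.

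**Whether another planned comparison helps.** The retrospective data come from the registry and supporting records at each hospital. A before/after comparison at an intervention hospital therefore changes the source together with the treatment. The Year 4 crossover at control hospitals appears to do the same.

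**Illustration of size.** All inputs here are assumptions: true retention 60% in both arms; probability that a delivered service is found in the records 95% per step (intervention) and 85% (control); an undocumented service counted as not done. Recorded retention with k independent exposed steps is 0.60 × c^k, where c is the per-step capture. The odds ratio (OR) is converted by d = ln(OR) × √3/π.

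| Assumption about gaps | Intervention | Control | OR | d |
|---|---|---|---|---|
| Four independent steps | 0.60 × 0.95^4 = 48.9% | 0.60 × 0.85^4 = 31.3% | 2.10 | 0.41 |
| DBS fully captured in both arms, three independent steps | 0.60 × 0.95^3 = 51.4% | 0.60 × 0.85^3 = 36.8% | 1.82 | 0.33 |
| Gaps fully correlated across steps | 0.60 × 0.95 = 57.0% | 0.60 × 0.85 = 51.0% | 1.27 | 0.13 |

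With a narrower gap, 95% versus 90% on four independent steps, the figures are 48.9% versus 39.4%, OR 1.47, d 0.21. Swapping the capture rates gives the same sizes with the opposite sign.

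**Across the article's retention range.** The Background cites retention of 32% to 74.7%. Take full capture in the intervention arm and three independent exposed steps in the control arm. The spurious difference is p × (1 − c^3), where p is true retention.

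- c = 0.95: 0.32 × 0.1426 = 4.6 points, up to 0.747 × 0.1426 = 10.7 points.
- c = 0.90: 0.32 × 0.271 = 8.7 points, up to 0.747 × 0.271 = 20.2 points.

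**The case against.** The strongest reply is that the control arm does not rest on one paper register. Four sources are searched, one of them a laboratory database, for the stated purpose of a parallel assessment. This stands. A reader might infer that every primary benchmark is affected, or that documentation cannot be separated from care at all. The documents do not support that, because the PCR and ART steps have independent records.

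Other stronger readings also fail:

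- **Bias must favour the HITSystem.** A four-source search may find control services that a single source would miss. The direction is open.
- **Alerts make staff enter dates.** The HIV infant tracking system section describes alerts that prompt care; no section says that they prompt data entry.
- **Undocumented services are scored as not done.** This is an inference from the retention definition, the index scoring and the statement under Statistical analyses that missing or lost dyads stay in. The article does not say how an undocumented service in a retained dyad is classified.
- **The artefact nearly equals the design effect of 0.44.** Only the four-independent-step case comes close. It applies the 85% to DBS, which the laboratory database covers, and assumes independence although one thin file can affect several steps. The Power and sample size section also does not define the metric of 0.44.

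Finally, this is a condensed article, and a concordance audit may exist in the full protocol. That limits the claim to what the article states. The point is still more than an omitted detail, because the article does state the measurement rule and the rule differs by arm.

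**Conclusion.** The point holds in a limited form. As described, outcome sources differ by arm, one of them is the intervention itself, and only that one has a described completeness review of service entries. Differential documentation can therefore appear as a treatment effect, in either direction, mainly on mother notification, OI prophylaxis and negative antibody re-tests at 9 and 18 months. It carries through to retention and the Care Index.

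Under the assumed 60% true retention and 95% versus 85% capture, the spurious d runs from about 0.13 to 0.41, depending on correlation between gaps and on DBS coverage. This rests on counting undocumented services as not done. Because the documents give no capture rate, these figures show that the problem could matter; they do not estimate the bias in this trial.

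**What to change.** - In both arms, take laboratory receipt and result dates from the central laboratory PCR database and ART start from CCC records.
- For notification, OI prophylaxis and re-tests, have the existing Research Coordinators apply the control-site cross-reference to intervention dyads, either all of them (up to 3 × 120 = 360) or a random sample.
- Report agreement between that review and HITSystem output, step by step.
- Add a sensitivity analysis of retention and the Care Index based on sources common to both arms.

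Chart-only abstraction should not become the primary source. At intervention hospitals the HITSystem takes the place of the registry notebook, so the remaining charts may be less complete and the bias could reverse.

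The cost is modest extra record-review time. It is an added in-trial task at the intervention hospitals, but for staff already in post: each intervention site has a Research Coordinator, and coordinators carried out the retrospective record review at each hospital. The selection criteria require hospitals to keep files for HIV-exposed infants. Trial status reports that enrollment was continuing and no analyses had been done, so the change could still be made before any analysis.

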##### EID retention

EID retention will be characterized as complete or incomplete. Incomplete EID care (loss to follow-up) is defined as one or more of the following: (1) DBS not collected, (2) mother not notified of result, (3) HIV-infected infant not started on ART, (4) HIV-uninfected infant not re-tested at 9 months, and 5) HIV-uninfected infant not re-tested at 18 months.

##### Time to ART initiation

In addition to calculating the proportion of HIV-infected infants who are initiated on ART, we will calculate the number of days between the date that the mother was notified of her infant’s HIV-positive status and the date the infant was initiated on ART.

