Although the guidelines provide clear objectives, challenges at every step in the EID cascade of care compromise the quality of EID services provided in Kenya and other low-resource settings [5, 7–9]. Infant testing often occurs after the recommended 6 weeks of age (average age of 3.1 months) [8, 10, 11], and turn-around times for results are typically quite long (average of 1–3 months) [10]. Retention throughout the recommended 18-month postnatal period is low (32–74.7 %) [8, 12] and less than one-third of Kenya’s HIV-infected infants are initiated on ART [6, 13]. Transportation, documentation, and communication challenges contribute to lost or delayed samples [5, 7], and a passive system for mother notification or follow-up leads to delayed care and missed opportunities to support retention [14–16]. Limited coordination between EID stakeholders limits accountability, efficiency, and linkage to treatment [5, 17]. In addition to these system-level challenges, mothers experience individual barriers that limit their full participation in the EID process (e.g., lack of: awareness of the existence or importance of EID services, resources for transportation, and fear of disclosure of their HIV status) [18, 19].

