Our study aims to evaluate the HIV Infant Tracking System (HITSystem), a web-based tool designed to address many of the barriers in current EID service provision in Kenya, with the ultimate goal of maximizing the quality of EID services. As a system-level intervention, it was not deemed feasible or acceptable to randomize at the individual level; therefore, randomization occurred at the site (hospital) level. Primary outcomes will be measured at the participant (mother-infant dyad) level and aggregated to report outcomes per hospital. The primary outcomes for efficacy of the HITSystem are retention through the EID Cascade of Care (measured by eight unique benchmarks between 0–18 months postnatal, including ART initiation among HIV-infected infants) (Table 1) and efficiency of services (turn-around times for EID services and ability to meet age and time-specific targets with the HITSystem compared to control sites where standard of care services are provided). Secondary outcomes are maternal and infant predictors of retention, postnatal period(s) at the highest risk for loss to follow-up, satisfaction among mothers and providers, and infant HIV infection status over time. Cost-effectiveness analyses will quantify resources required to implement the HITSystem versus standard EID services and calculate potential short and long-term costs averted by this intervention to inform scale-up and sustainability.

**Table 1 Tab1:** HITSystem targets: eight time-sensitive EID interventions

1.Initiation of OI prophylaxis at 6 weeks
2.Collect dried blood spot (DBS) for PCR test by 6 weeks
3.Receipt of DBS at lab within 10 days of collection
4.Return of PCR results from lab within 2 weeks
5.Notify mother within 2 weeks of the EID provider receiving results
6.Initiate all HIV-infected infants on ART within 4 weeks of notifying the mother
7.Retest all HIV-uninfected infants at 9 months, initiate ART w/in 4 weeks if applicable^a^
8.Retest all HIV-uninfected infants at 18 months, initiate ART w/in 4 weeks if applicable^a^

^a^Re-testing indicated at these time points or 6 weeks after cessation of breastfeeding

Greater detail regarding the 8 intervention points and the HITSystem process has been previously published. [21]

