##### Turn-around time of infant test results

We will calculate the number of weeks between the date that the dried blood spot sample was collected and the date that the result was made available to the hospital. We will also calculate the time (in weeks) to notifying the mother of her infant’s test results.

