### Statistical analyses

We will calculate descriptive statistics to compare outcomes for each of the eight time-sensitive EID outcomes by intervention or control hospitals. In our preliminary analyses, we will estimate general linear models to determine whether there are pre-intervention differences across conditions and hospitals—for any of the measures we will be using as predictors or outcomes. Any significantly different variables will be included as covariates in our analytic models. Given attrition (not completing all 8 EID intervention points) is a major outcome of interest, we will predict and describe it. Hence, even “missing” or “lost” dyads will be included in outcome measures.

To predict patterns of EID utilization among HIV-exposed infants, we will first identify bivariate correlates of the main outcome: EID retention. Correlations between incomplete EID retention and possible predictors (e.g., infant sex, maternal disclosure, etc.) will be conducted and tested for significance using Phi, Point Biserial, or Spearman Rho statistics depending on the measurement level of each predictor. We will then include variables that are significantly correlated with EID retention in the generalized linear mixed model and use a stepwise approach to identify a parsimonious list of predictors, controlling for the correlation of observations within cluster with random effects. We will follow the same steps to assess correlates of the 5 unique EID intervention points that comprise the summative incomplete EID retention variable:(1) DBS not collected, (2) mother not notified of result, (3) HIV+ infant not started on ART, (4) HIV infant not re-tested at 9 months, and (5) HIV infant not re-tested at 18 months. To identify the most vulnerable time periods for EID retention, we will use survival analysis with random effects [23] to determine how long infants stay in EID care and identify time periods when significant drops in EID retention occur. Visual EID retention curves will illustrate differences in EID care retention at various time points throughout the 18-month EID period. Comparisons between intervention and control participants will highlight the impact of the HITSystem at various time points in EID utilization.

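### Time to ART, result turn-around and time to notification are defined so that dyads who never complete the step cannot enter them, despite the stated aim of keeping lost dyads in the outcome measures

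*Protocol article*

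**What the plan says.** Three interval measures are defined under Primary EID outcomes.

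- **Time to ART initiation.** "In addition to calculating the proportion of HIV-infected infants who are initiated on ART", the article says, "we will calculate the number of days between the date that the mother was notified" of a positive result and the date ART began.
- **Result turn-around.** The article states "We will calculate the number of weeks between the date that the dried blood spot sample was collected", with the end point being when the hospital could see the result.
- **Time to notification**, in the same section: "We will also calculate the time (in weeks) to notifying the mother of her infant’s test results". The start date is not named.

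Background places turn-around among the primary outcomes, as "efficiency of services (turn-around times for EID services and ability to meet age and time-specific targets with the HITSystem compared to control sites". The Abstract's shorter list of primary outcomes has the proportion of services delivered on time instead.

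On lost dyads, Statistical analyses says in general terms that they "dyads will be included in outcome measures". Survival analysis with random effects is assigned there to length of stay in EID care. The multilevel models cover the Index and its sub-scales, the infant's age at first PCR, and the proportions re-tested by 9 and by 18 months. None of the three intervals is in either list.

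**The concern.** A difference between two dates exists only when both dates exist. Whether the second date ever arises is a post-randomisation event, and it is what the HITSystem is built to change through laboratory alerts, text messages and tracing. The trial hypothesises higher retention at intervention sites, and Background says that weaknesses in the present system "contribute to lost or delayed samples".

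If the intervals are compared as defined, each arm contributes only the dyads that got through the step. An arm that traces slow or hard-to-reach dyads adds long intervals to its own summary, while the other arm's failures leave no interval at all. On an outcome that the article calls primary, a better system could then look no faster, or slower.

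Time to ART has a second condition. Its clock starts at notification, so an infected infant whose mother was never notified lacks a start date as well as an end date, and delay before notification does not enter this measure.

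**Working it through.** The article gives no figure for these intervals, so there is none to reproduce. The check has two parts.

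**1. Where non-completers are counted**

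| Failure | Retention | ART proportion | Optimal EID Care Index | Raw interval |
|---|---|---|---|---|
| Sample lost, no result | not a listed criterion itself; counts once the mother is not notified | – | 0 for return of results | no value |
| Mother never notified | incomplete | – | 0 for notification | no value |
| Infected infant never treated | incomplete | counted as not started | 0 for ART | no value |

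The Index gives "0 point (never completed), 1 point (off-time completion), or 2 points (on-time completion" for each service. Only the last column loses these dyads, and neither the survival analysis nor the list of modelled outcomes brings them back.

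**2. How far a both-dates-only comparison can mislead**

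All inputs here are assumptions; none comes from the article. Let weeks to notification be exponential with mean μ, and let contact end at week L.

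- Proportion notified: F = 1 − exp(−L/μ)
- Median among those notified: −μ ln(1 − F/2)
- Median in all dyads, if contact never ended: μ ln 2

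*No true difference.* Take μ = 8 in both arms, so the underlying median is 8 × 0.693 = 5.55 weeks. Intervention contact lasts 26 weeks: F = 1 − exp(−26/8) = 0.96, and the median among those notified is 5.24 weeks.

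| Control contact ends (week) | Control notified | Control median, notified only | Intervention median, notified only |
|---|---|---|---|
| 4 | 39% | 1.75 | 5.24 |
| 6 | 53% | 2.45 | 5.24 |
| 8 | 63% | 3.04 | 5.24 |
| 12 | 78% | 3.93 | 5.24 |

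Control looks faster on every row although the rates are equal. With μ at 6, 8 or 10 the control medians run from 1.7 to 4.3 weeks and the intervention medians from 4.1 to 6.2.

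If un-notified dyads stay in the denominator, the two cumulative curves coincide until control contact ends, and the control curve then goes flat at the percentage shown. The control median is 5.55 weeks where its curve passes 50% (rows 6, 8 and 12) and is not reached in row 4.

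*Intervention truly faster.* Take μ = 6 against 10. The underlying medians are 4.16 and 6.93 weeks, an advantage of 6.93 − 4.16 = 2.77 weeks. Among those notified, the intervention median is 4.08 and the control medians are 1.80, 2.56, 3.22 and 4.30 for contact ending at week 4, 6, 8 and 12. The intervention therefore appears 4.08 − 1.80 = 2.28 weeks slower at one end and 4.30 − 4.08 = 0.22 weeks faster at the other. With all dyads kept, the proportions notified by week 4 are 1 − exp(−4/6) = 49% and 1 − exp(−4/10) = 33%, which is the right order.

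**The case against.** The strongest reply is that the article nowhere restricts the analysis to dyads with both dates. A reader might infer that it has chosen to drop non-completers and so forfeits randomisation for its primary comparisons. The text does not support that. It says the opposite in general terms, and the failures are scored in the retention outcome, in the ART proportion named in the same sentence as time to ART, and in the Index. The Index sub-scales already give an on-time comparison that keeps everyone. This part of the reply stands, and it limits the point to the raw intervals.

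Three further replies have weight:

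- Starting the ART clock at notification matches Table 1, which sets its ART target from that date. It is a legitimate measure of one step, and earlier delay is measured in the turn-around section and scored in the Index.
- The bias needs loss that is related to slowness. If samples go missing regardless of how fast they would have been processed, turn-around among returned samples is not distorted.
- The article is condensed, and a censoring rule may stand in the full protocol or analysis plan.

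The last reply does not dispose of the point. What is at issue is a definition that the article does fix: a two-date difference cannot take in a dyad with one date, so the general statement on lost dyads cannot be met by these measures as written.

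**Conclusion.** The point holds for the three raw intervals and no further. As defined they exist only for dyads who completed the step. That does not fit the statement that lost dyads are included, and it matters because turn-around times are named within a primary outcome. Retention, the ART proportion and the Index are unaffected.

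The size cannot be computed from the documents. The illustration shows that hiding or reversal of a benefit is possible, not that it will occur. It rests on exponential times, on assumed means of 6 to 10 weeks, and on control contact ending at 4 to 12 weeks against 26 weeks for intervention. A reader should not take from it that the HITSystem will look slower by any stated amount, since smaller differences in completion give smaller distortion. The planned ART proportion, shown beside time to ART, would also alert a reader to unequal completion for that interval.

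**What to change.** State in the analysis plan that the intervals are compared between arms as time-to-event outcomes among all dyads at risk:

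- DBS collection to result available, and DBS collection to mother notified, in every dyad with a sample collected;
- in HIV-infected infants, DBS collection or result date to ART start.

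Censor at end of follow-up or transfer and treat death as a competing event. A dyad that simply stops attending stays in the risk set as not yet notified or not yet treated. Report cumulative incidence by arm, with the hospital random effect already planned for retention.

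Keep notification-to-ART days and all completers-only intervals as descriptive, each beside the proportion completing the step.

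One limit remains. An infant whose sample was lost before testing cannot be classed as infected, so the ART analysis still depends on a result having been obtained. The collection-to-result curve shows how often that failed in each arm.

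The cost is analysis wording, a little more analysis work and some overlap with the Index. The article says that service dates, outcomes and reasons for discharge are already collected and that no analysis had yet been run.
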